#### Cost-effectiveness Analysis

In our cost-effectiveness analysis, we will compare costs and health outcomes between stepped care ICBT and gold-standard CBT. Costs will be collected from 2 different perspectives: a health care organization perspective and a societal perspective. Costs within the health care organization perspective include recorded therapist time in the ICBT treatment and on face-to-face CBT sessions (including time for preparation and traveling), telephone calls, and administration. In the analysis from a societal perspective, other health care costs (other health care utilization and medication use) as well as indirect costs (eg, informal care, productivity loss associated with school and work absenteeism) captured by the TiC-P will be included.^38^ Our hypothesis is that there will be a difference between the 2 groups in treatment costs from the health care organization perspective, but we expect no difference in other costs.

Two types of analyses will be conducted on each of the 2 perspectives: a cost-effectiveness analysis and a cost-utility analysis. In the cost-effectiveness analysis, both number of responders and remitters at primary end point (6-month follow-up) will be used as the health outcome. We will use expert consensus criteria to define treatment response and remission.^30^ A responder is defined as at least 35% reduction on the CY-BOCS and a CGI-I score of 1 (very much improved) or 2 (much improved). Remission is defined as a score of less than or equal to 12 on the CY-BOCS and a CGI-S rating of 1 (normal, not at all ill) or 2 (borderline mentally ill). In the cost-utility analysis, the outcome will be quality-adjusted life years, according to international standards for cost-effectiveness analyses.^47,48^ Quality-adjusted life-years will be calculated using the area under the curve method.^49^ Costs will be estimated by appropriate regression analyses testing alternative link functions and distributions.^50^ Nonparametric bootstrapping with 5000 iterations will be carried out, pairing up differences in costs with differences in outcomes. As a global cost-effectiveness estimate, we will present the incremental cost-effectiveness ratio (difference in costs between the 2 groups divided by the difference in effect),^51^ as well as a visual presentation of cost-effectiveness planes. The time frames for the cost-effectiveness analyses will be from baseline to the 6-month follow-up, and from baseline to the 1-year follow-up.

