## Introduction

Cognitive behavior therapy (CBT) is regarded as the gold-standard treatment for pediatric obsessive-compulsive disorder (OCD)^1,2^ and has consistently shown large effect sizes compared with both wait-list (*g* = 1.53) and various active comparators (*g* = 0.93)^3^ as well as sustained long-term effects.^4^ Furthermore, CBT is an effective augmentation treatment for patients showing suboptimal response to initial courses of both serotonin reuptake inhibitors^5^ and CBT.^6^ Unfortunately, suitably trained CBT therapists specializing in OCD are scarce and typically concentrated in large urban areas, and it is estimated that many patients do not have access to CBT.^7,8,9,10^ One way to increase the availability of CBT is to remotely deliver it online without the need to attend in-clinic sessions with a therapist.^11^ Our research group has developed a therapist-guided internet-delivered CBT (ICBT) program for youth with OCD called *BIP OCD*. The treatment is primarily self-guided, with assistance from parents or legal guardians, and supported by a designated therapist who communicates with both the child and the parent through the entire treatment. The BIP OCD program has to date been evaluated in 2 open pilot studies in both children^12^ and adolescents^13^ that showed high acceptability and safety and promising results. A subsequent randomized clinical trial including 67 patients demonstrated superiority and cost-effectiveness of BIP OCD against a wait-list control.^14,15^ Interestingly, the effects of ICBT were slightly weaker than expected but continued beyond the primary end point, with patients experiencing additional symptom improvement at the 3-month follow-up. This delayed improvement phenomenon has also been observed in other ICBT trials.^16,17^ As participants in these trials were primarily self-referred^12,13,14^ and may therefore constitute a selected group of individuals (eg, highly educated, more motivated), the generalizability of these findings to regular clinic-referred patients is currently unclear.

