## Methods

### Study Design

The study is a 2-site randomized clinical noninferiority trial for children and adolescents with OCD. Participants randomized to stepped care ICBT first receive ICBT for 16 weeks; patients classed as nonresponders at the 3-month follow-up are offered a course of face-to-face CBT for up to 12 weeks. Participants randomized to the gold standard treatment receive face-to-face CBT for 16 weeks; as in the stepped care group, patients classed as nonresponders at the 3-month follow-up are offered additional sessions of face-to-face CBT for up to 12 weeks. The full trial protocol is available in the Supplement.

The primary end point is 6 months after the end of the first course of treatment (6-month follow-up). Long-term effects will be investigated 1, 2, and 5 years after treatment completion. The trial design is graphically summarized in the Figure.

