### Assessment Points

The assessments occur at predetermined points after randomization and are independent of the treatment progress. The primary end point is at 6-month follow-up. All clinician measures and self- and parent-reported questionnaires are administered at baseline, after treatment, and at 3-month, 6-month, and 1-year follow-ups. Self- and parent-administered measures of OCD symptom severity are also administered weekly during the first 16 weeks of treatment. Additional clinician follow-up assessments are conducted after 2 and 5 years via telephone. Changes in psychotropic medication and additional psychological treatment are monitored and documented throughout the study period.

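### The baseline-to-1-year cost-effectiveness analysis has no matching effect: responder and remitter status is defined only at the 6-month follow-up

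*Protocol article*

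**What the plan says.** All of the wording at issue is in the protocol article, under Cost-effectiveness Analysis.

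- **Effect measure.** "both number of responders and remitters at primary end point (6-month follow-up) will be used as the health outcome". Response combines a percentage fall in CY-BOCS with a CGI-I rating. Remission combines a CY-BOCS cut-off with a CGI-S rating. No other visit is named for either.
- **Time frames.** The analyses run "from baseline to the 6-month follow-up, and from baseline to the 1-year follow-up".
- **Combination.** The bootstrap works by "pairing up differences in costs with differences in outcomes", and the summary is the cost difference divided by the effect difference, shown also on cost-effectiveness planes.
- **Second type of analysis.** The cost-utility analysis uses quality-adjusted life-years by area under the curve.

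Under Assessment Points: "All clinician measures and self- and parent-reported questionnaires are administered at baseline, after treatment, and at 3-month, 6-month, and 1-year follow-ups". Table 2 confirms that CY-BOCS, CGI-S, CGI-I, CHU9D and TiC-P are all taken at 1 year.

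**The concern.** A cost-effectiveness ratio needs its numerator and denominator to cover the same period. Here the effect is tied to a named visit, and a second time frame is then added that ends at a later visit. A statistician who follows the text will accumulate costs to 1 year and divide by the difference in responders at 6 months.

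A patient who responds at 6 months and has relapsed by 1 year still counts as a responder in the 1-year analysis. A patient who first meets the criteria at 1 year does not count. If the arms differ in either respect, the 1-year ratio and plane will not show it, although showing how cost-effectiveness holds up beyond 6 months is the evident purpose of a second time frame. Cost-effectiveness is part of the trial's main question, so the 1-year result is likely to be quoted.

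**Working it through.** The plan gives no figure to reproduce. The check is a timeline, a comparison of what each analysis can capture, and an illustration on assumed rates.

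**1. Timeline (weeks from the start of treatment)**

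- First course, Study Design: "Participants randomized to stepped care ICBT first receive ICBT for 16 weeks". The comparator course is also 16 weeks.
- The 6-month follow-up is 6 months after the end of the first course (Study Design): 16 + 26 = week 42.
- 1-year follow-up, Study Design: "Long-term effects will be investigated 1, 2, and 5 years after treatment completion", so 16 + 52 = week 68. This takes treatment completion to mean the end of the first 16-week course. Assessment Points supports that, because visits are fixed from randomization and do not move with treatment progress.
- Gap: 68 − 42 = 26 weeks, and 26/68 = 0.38.

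Thus 38% of the calendar time in the second frame lies after the effect has been measured. This is a share of time, not of costs.

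**2. What each analysis can capture in weeks 42 to 68**

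| Component | Source | Can it change after week 42? |
|---|---|---|
| Responder/remitter effect | Cost-effectiveness Analysis | No, as written |
| QALYs, area under the curve | Cost-effectiveness Analysis; CHU9D at 1 year in Table 2 | Yes |
| Health care organization costs (therapist time and related items) | Cost-effectiveness Analysis; extra CBT falls between the 3- and 6-month follow-ups (Nonresponders) | Little; planned trial treatment is over |
| Societal costs (TiC-P) | Secondary Outcome Measures: 3-month recall | Yes, but the 1-year form reaches back only to about 68 − 13 = week 55 |

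In the societal perspective, costs move on while the effect stands still. In the health care organization perspective, neither moves much, so the 1-year responder ratio would largely repeat the 6-month one.

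**3. Illustration of what a fixed effect can miss**

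The document gives no response, relapse or late-response rates, so every input here is an assumption. Take 6-month response of 60% in stepped care and 65% in face-to-face CBT. The difference is −5.0 points. For each arm,

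1-year response = (6-month response) × (1 − relapse) + (1 − 6-month response) × (late response).

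- 5% relapse and 5% late response in both arms: stepped care 0.60 × 0.95 + 0.40 × 0.05 = 0.590; CBT 0.65 × 0.95 + 0.35 × 0.05 = 0.635; difference −4.5 points.
- Relapse raised to 15% in stepped care only: 0.60 × 0.85 + 0.40 × 0.05 = 0.530; difference from 0.635 is −10.5 points.
- Late response raised to 20% in stepped care only: 0.60 × 0.95 + 0.40 × 0.20 = 0.650; difference from 0.635 is +1.5 points.

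With the effect fixed at 6 months, the denominator is −5.0 in all three cases. The ratio is sensitive because a small difference in effect is divided into the cost difference. On these inputs even its sign can change. The illustration shows the mechanism and does not estimate its size in this trial.

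**The case against.** **The pairing is implied, not stated.** No sentence says that 1-year costs will be divided by 6-month status. A time frame for an analysis that pairs costs with outcomes could be meant to govern both, and the 1-year ratings exist. The investigators may well have intended 1-year status. This stands as a limit on the wording. It does not remove the point, because the section names a visit for the effect and does not release it for the second frame.

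**The article is a condensed text.** Study Design points to a full protocol in a supplement that is not shown. Detail left to that document would be no finding. Here, however, the article itself fixes the time point, and what it fixes does not fit its own second time frame.

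**Durability is examined elsewhere.** The QALY analysis can reach 1 year under both perspectives, and the Outcome Data section plans a separate analysis of long-term maintenance. Both are true and confine the defect. Neither repairs the 1-year responder/remitter ratio.

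**Anchoring at 6 months is defensible.** It is the last blinded assessment (Blinding), and stable medication is requested only until then (Participants). That is a sound reason to keep 6-month status for the 6-month frame, or to drop the 1-year responder analysis. It is no reason to combine that status with 1-year costs.

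**Stronger readings that the document does not support.**

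- A reader might infer that any relapse or late gain after 6 months changes costs. Planned therapist costs largely end by 6 months, the 1-year TiC-P as described leaves about weeks 42 to 55 uncovered, and nothing says that late improvement raises cost.
- A reader might take the Introduction's remark that "the effects of ICBT were slightly weaker than expected but continued beyond the primary end point" as evidence of change after this trial's 6-month visit. The further gain it describes was seen at a 3-month follow-up, a point that the 6-month effect here already includes.

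**Conclusion.** The point holds in a limited form. As written, the baseline-to-1-year responder/remitter analysis uses an effect measured 26 weeks before its time frame ends, so it cannot reflect a between-arm difference in relapse or late response after 6 months. It matters mainly in the societal perspective. The QALY analysis, the 6-month economic analysis and the primary noninferiority analysis are not affected.

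The 26 weeks and the 38% follow from the document's own durations, given that 1 year is counted from the end of the first course. The consequence for the ratio cannot be derived from the document, since it depends on relapse and late-response rates that are not given. A reader might infer that the 1-year result is bound to be biased in a known direction. The text does not support that: the error could go either way, and would be small if the two arms change alike.

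**What to change.** State which visit supplies the effect for each time frame. For the frame from baseline to the 1-year follow-up, define responders and remitters by the same criteria at the 1-year visit, and keep 6-month status for the 6-month frame. Alternatively, limit the responder/remitter analysis to the 6-month frame and let the QALY analysis carry the 1-year frame.

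Either choice takes one sentence and no new data. If 1-year status is used, the plan should say that the ratings are unblinded, that medication stability is requested only until the 6-month follow-up, and that attrition may be somewhat higher by then.

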Secondary clinician-rated outcome measures are the CGI Severity and Improvement scales (CGI-S and CGI-I)^23^ and CGAS.^24^ Severity of OCD symptoms is measured using the child-rated Obsessive-Compulsive Inventory–Child Version (OCI-CV)^31^ and the Children's Obsessional Compulsive Inventory Revised–Parent version (ChOCI-R-P).^32^ Family accommodation behaviors are measured using the Family Accommodation Scale–Self Rated (FAS-SR).^33^ Impairment of functioning due to OCD is assessed using the Work and Social Adjustment Scale–Youth version and Parent version (WSAS-Y and WSAS-P), which are adaptations of the Work and Social Adjustment Scale.^34^ Depressive symptoms are assessed using the short version of the Mood and Feelings Questionnaire (MFQ).^35^ The Insomnia Severity Index (ISI)^36^ is used to quantify the severity of insomnia. The Child Health Utility 9D (CHU9D)^37^ is used as a measure of quality of life and for the estimation of quality-adjusted life years. The Trimbos/iMTA Questionnaire for Costs Associated With Psychiatric Illness (TiC-P),^38^ which measures resource use of health care, social support and assistance, medication use, informal care by parents, and school and work absenteeism over the last 3-month period, is administered to the parents. The Autism Spectrum Quotient (AQ-10)^39^ is used as a baseline measure of autistic symptoms rated by the parent. Other measures are the Treatment Credibility and Expectancy Scale (TCES)^40^ to measure how credible participants perceive the treatment to be, the Working Alliance Inventory (WAI)^41^ to measure working alliance, and the Client Satisfaction Questionnaire (CSQ-8)^42^ to assess participants’ satisfaction with treatment. To measure treatment adherence, the Patient EX/RP Adherence Scale (PEAS)^43^ is used to investigate the amount of exposure and response prevention exercises performed weekly (administered as both a clinician-rated and self-reported measure during face-to-face CBT and as a self-rated version during ICBT), and the clinician-rated Internet Intervention Patient Adherence Scale (iiPAS)^44^ is used only in the ICBT group. To investigate the role of parental behaviors in relation to treatment outcome, questions about parental strategies are administered every week during treatment.

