#### Outcome Data

The only previous pediatric OCD trial using a noninferiority design used −5 points on the primary outcome measure (CY-BOCS) as a noninferiority margin with an SD of 8.^28^ In the present study, we set the noninferiority margin to −4 points to gain greater precision. The noninferiority analysis will be based on the CY-BOCS score at the primary end point (6-month follow-up) and determined by the confidence interval around the mean difference between the 2 groups. The estimated enrollment is 152 participants, which gives an estimated power greater than 95%, allowing for possible data attrition (10% based on experience from our previous trials). The power is estimated based on each participant being observed at 4 points (baseline, after treatment, 3-month follow-up, and 6-month follow-up). We used a linear random intercept model with 1000 bootstrap samples using the following values, which were based on individual-level data from a previous study of therapist-guided ICBT for adolescents with OCD that used 3 repeated observations^14^: intercept (22.45), slope (−0.37 per week), SD of the random effect (4.03), and SD of the residual error (3.94). In other words, if the stepped care ICBT approach is truly noninferior to the gold-standard treatment, 152 patients will give an estimated probability greater than 95% that the upper limit of a 1-sided 95% confidence interval (or, equivalently, a 90% 2-sided confidence interval) will be below the noninferiority limit of 4 points on the CY-BOCS. No specific noninferiority margin is defined for the secondary outcome measures, but we expect no statistically significant difference between the groups on these measures.

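### No baseline-utility adjustment is stated for the QALY difference; without it the cost-utility comparison stays valid but is less precise than the collected data allow

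*Protocol article*

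**What the plan says.** The relevant statements in the protocol article are these.

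- Secondary Outcome Measures: the CHU9D "is used as a measure of quality of life and for the estimation of quality-adjusted life years".
- Assessment Points: "All clinician measures and self- and parent-reported questionnaires are administered at baseline, after treatment, and at 3-month, 6-month, and 1-year follow-ups". Table 2 marks the CHU9D at the same five points, so a baseline utility exists for use as a covariate.
- Cost-effectiveness Analysis, QALYs: "Quality-adjusted life-years will be calculated using the area under the curve method".
- Same section, horizons: "The time frames for the cost-effectiveness analyses will be from baseline to the 6-month follow-up, and from baseline to the 1-year follow-up". The baseline value is therefore part of the area.
- Same section, costs: "Costs will be estimated by appropriate regression analyses testing alternative link functions and distributions". No regression is named for QALYs.
- Same section, uncertainty: "Nonparametric bootstrapping with 5000 iterations will be carried out, pairing up differences in costs with differences in outcomes". The incremental cost-effectiveness ratio (ICER) is then the cost difference over the effect difference.

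Randomization is stratified by referral source and age group, not by utility. The article neither states nor rules out baseline adjustment of QALYs, and it points to a full protocol in a supplement that is not available here.

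**The concern.** The area under the utility curve begins with a value measured before randomization, which treatment cannot change. That value also predicts every later utility. If the arms differ by chance at baseline, the difference enters an unadjusted QALY comparison twice: through its own share of the area and through its persistence into later visits.

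The steps in the Cost-effectiveness Analysis section can be carried out exactly as printed, and doing so gives a simple difference in mean QALYs. The mixed model under Outcome Data does not fill the gap. It is a repeated-measures model, and an area-under-the-curve QALY is one number per patient.

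What is at stake is precision. Cost-effectiveness is half of the trial's stated question, and the article expects no significant between-group difference on secondary measures. The QALY difference is then likely to be small, and avoidable noise in it widens the bootstrap cloud on the cost-effectiveness plane.

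**Working it through.** **1. The plan's own figure.** The article gives no figure for the QALY comparison. Its only related figure is the power statement: "The estimated enrollment is 152 participants, which gives an estimated power greater than 95%, allowing for possible data attrition". From the stated components, SD = sqrt(4.03² + 3.94²) = 5.64. With 76 × 0.9 = 68.4, about 68 per arm, SE = 5.64 × sqrt(2/68) = 0.967. Then 4/0.967 − 1.645 = 2.49, which is 99.4% power for a single time point and agrees with the article. The same components imply a within-person correlation of 4.03²/(4.03² + 3.94²) = 0.51. That is for the CY-BOCS and is only a rough guide for the CHU9D.

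**2. Weights in the area.** A 16-week first course, with follow-ups counted from its end, puts the visits at about weeks 0, 16, 29, 42 and 68. Trapezoid weights in weeks are:

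- to the 6-month follow-up: 8, 14.5, 13, 6.5 (sum 42); baseline share 8/42 = 19%
- to the 1-year follow-up: 8, 14.5, 13, 19.5, 13 (sum 68); baseline share 8/68 = 12%

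**3. Formulas.** Assume equal SD at each visit and the same correlation ρ between any two visits. With weights w, sum T and baseline weight 8, in units of SD²:

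- variance of the area: V = (1 − ρ)Σw² + ρT²
- covariance with baseline: C = 8 + ρ(T − 8)
- variance explained by baseline: R² = C²/V
- unadjusted SE over adjusted SE = 1/sqrt(1 − R²)

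Σw² is 485.5 to 6 months and 992.5 to 1 year.

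| Horizon | ρ | V | C | R² | Unadjusted SE larger by |
|---|---|---|---|---|---|
| 6 months | 0.3 | 869.05 | 18.2 | 0.38 | 27% |
| 6 months | 0.5 | 1124.75 | 25 | 0.56 | 50% |
| 6 months | 0.8 | 1508.3 | 35.2 | 0.82 | 137% |
| 1 year | 0.3 | 2081.95 | 26 | 0.32 | 22% |
| 1 year | 0.5 | 2808.25 | 38 | 0.51 | 43% |
| 1 year | 0.8 | 3897.7 | 56 | 0.80 | 126% |

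**4. Absolute size, 6 months.** Assume a utility SD of 0.15, ρ = 0.5 and 68.4 per arm:

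- unadjusted SE = 0.15 × sqrt(1124.75)/52 × sqrt(2/68.4) = 0.0165 QALY
- adjusted SE = 0.0165 × sqrt(1 − 0.56) = 0.0110 QALY
- one SE of baseline imbalance = 0.15 × sqrt(2/68.4) = 0.0257 utility, which moves the unadjusted difference by 25/52 × 0.0257 = 0.0123 QALY

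The parts add up: 0.0110² + 0.0123² = 0.0165². The excess is the imbalance component.

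**5. Where the shift comes from.** A baseline imbalance of 0.03 moves the 6-month difference by 8/52 × 0.03 = 0.0046 QALY through its direct weight. With persistence counted, the shift is 18.2/52 × 0.03 = 0.0105 at ρ = 0.3 and 35.2/52 × 0.03 = 0.0203 at ρ = 0.8. Most of it comes from correlation with later visits.

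**6. Validity.** In 20,000 simulated trials with no true difference (ρ = 0.51, SD 0.15, 68 per arm), the mean unadjusted difference was −0.0001. Two-sided type I error was 4.9% both with and without adjustment, and the ratio of standard errors was 1.51.

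**The case against.** The strongest objection is that silence is being read as a decision. The area-under-the-curve sentence says how each patient's QALY is formed, not how the arms are compared. Regressing those QALYs on baseline utility would still use that method, and the bootstrapped differences could be adjusted ones. The article lists no covariates for the cost regression either, and such detail may stand in the full protocol. This objection stands in part. A reader might infer that the authors chose a raw, unadjusted comparison, and the article does not support that. What remains is that the section gives the estimation steps in order, assigns regression to costs alone, and yields an unadjusted difference if followed.

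A reader might also infer that the QALY result would be biased or its type I error inflated. Neither holds, as step 6 shows. The shift from imbalance is bias only conditional on the imbalance observed, and a bootstrap of unadjusted differences already includes that variability in its spread.

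Nor does adjustment settle the quadrant of the cost-effectiveness plane. If the true QALY difference is near zero, sampling error decides its sign with or without adjustment. Adjustment narrows the spread.

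**Conclusion.** The point holds as a free gain in precision, not as an error that invalidates an analysis. If the article's steps are followed as printed, the 6-month QALY difference has a standard error about 50% larger than the baseline-adjusted one at a visit correlation of 0.5, and 27% to 137% larger over 0.3 to 0.8. On the 1-year horizon the range is 22% to 126%.

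These ratios do not depend on the utility SD, but the absolute figures do. They rest on an assumed CHU9D correlation that is equal between all visits, on nominal visit weeks, and, for the absolute figures, on an assumed SD of 0.15 and the article's 10% attrition applied to the CHU9D. If correlation fades with time since baseline, the gain is smaller.

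The effect is confined to the cost-utility analysis. The CY-BOCS noninferiority test and the cost-effectiveness analyses on responders and remitters do not use this quantity.

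**What to change.** Add to the Cost-effectiveness Analysis section, or confirm if the full protocol already contains it, wording such as: *The between-group difference in area-under-the-curve QALYs will be estimated by regression of QALYs on treatment group and baseline CHU9D utility. This regression will be refitted in each of the 5000 bootstrap samples, and the resulting difference paired with the cost difference from the same sample.*

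The cost is a sentence or two and a few lines of code. Baseline CHU9D is already collected, so no new data are needed. Primary end point results were still awaited when the article was written. Fixing the choice before they are seen also removes a later choice between adjusted and unadjusted estimates.
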